### Instruments used

The instruments used for this study are described in detail in Table 1. Each instrument is outlined based on its purpose and the specific data it collects.

**Table 1 pone.0324565.t001:** Instruments used and timepoints.

No	Instruments	Description	Instruments to be completed by	Time-points
1	Baseline demographic questionnaire	to collect doctors’ demographic data	Physicians, patients	Baseline
3	STOPPFall	to analyse patients’ medication list for any PIMs.	Pharmacist	Baseline
4	Patient-Medication Adherence Instrument (PMAI-9)	to assess patients’ adherence towards their medications from the patient’s perspectives	Patients	Baseline, 3 month, 6 month
5	Healthcare-Professional-Medication Adherence Instrument (HMAI-9)	to assess patients’ adherence towards their medications from and HCP’s perspectives	Pharmacist	Baseline, 3 month, 6 month
6	Patient assessment form	to document the medical history, medication history, falls history, syncope symptoms and its precipitating factors, clinical frailty scale score and deprescribing intervention in older persons.	Pharmacist	Baseline, 3 month, 6 month
7	Ambulatory Care Patient Satisfaction Questionnaire (ACPSQ)	to assess quality of pharmacy services delivered by the pharmacist.	Patients	Baseline
8	Physician–Pharmacist Collaborative Index (PPCI)	to assess the professional exchanges between doctors and the pharmacist.	Physicians	Baseline
9	Falls diary	to record any falls occurrence in older persons. Prompts will be provided in the falls diaries, which include how and when a fall occurred, or if there were injuries sustained after their fall.	Patients	Daily (Diary returns at 3 month and 6 month)

### Data analysis

Data will be analysed using the Statistical Package for the Social Sciences (SPSS) version 21 (IBM^TM^, Armonk, New York, United States). A normality test will be performed. Descriptive statistics will be presented as percentages and frequencies, whilst continuous variables will be calculated using means and standard deviation. Raw, unadjusted, outcomes data will be presented. No hypothesis testing will be conducted for baseline variables given that any differences would have occurred at random. For comparisons of subsequent follow-up data, categorical variables will be analysed using the chi-squared test while the independent t-test will be used for continuous variables.

Outcomes analysis will be conducted on an intention-to-treat basis. All outcome variables that contain less than 10% missing data, will be considered missing at random and no replacement will be conducted. For outcome variables with greater than 10% missing data, missing data analyses will be conducted. Data missing not at random will be replaced using multiple imputations. The primary outcome measurement of the total number of medications per person will represent a continuous variable. Between-group and within-group analyses will be conducted using repeated measures analysis of variance. The remaining outcome variables will be handled according to whether each variable is categorical or continuous, normally or non-normality distributed, and the number of observations obtained. Variables with single measurements will be compared using logistics or linear regression analysis while those with multiple measurements with repeated measures analysis of variance or general estimating equations. Unadjusted analyses will first be presented. Potential confounders will be selected using available published evidence and clinical judgement.

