### Sample size calculation

Sample size was calculated using the Open Source Epidemiologic Statistics for Public Health (OpenEpi version 3.01) [21]. A search of published literature found that the mean change in the number of prescribed medications at 12 months was −1.9 ± 4.1 in intervention group participants and +0.1 ± 3.5 in control group participants [22]. Hence, the minimum number of participants needed with a two-sided confidence level of 95%, and 80% power will be at least 58 participants in each group [21]. Assuming a 20% attrition rate [23], the total number of 70 participants will be recruited to each arm.

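### The missing-data rule ties multiple imputation to data missing not at random and lets a 10% cut-off declare the mechanism, so the intention-to-treat estimate can be biased

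*Protocol article*

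**What the plan says.** All the rules stand in the Data analysis section of the protocol article.

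- Principle: "Outcomes analysis will be conducted on an intention-to-treat basis".
- Under 10% missing: "All outcome variables that contain less than 10% missing data, will be considered missing at random and no replacement will be conducted".
- Over 10% missing: "For outcome variables with greater than 10% missing data, missing data analyses will be conducted". These analyses are not described.
- Use of imputation: "Data missing not at random will be replaced using multiple imputations". No imputation model, departure from MAR or sensitivity analysis is named.
- Model for the primary outcome, the total number of medications: "Between-group and within-group analyses will be conducted using repeated measures analysis of variance".

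The Sample size calculation section plans on dropout: "Assuming a 20% attrition rate [23], the total number of 70 participants will be recruited to each arm". The Procedure section takes the medication count at 3 and 6 months from the electronic medical record (EMR) as well as from telephone interviews.

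**The concern.** Three elements of the rule do not fit together.

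1. **Method and mechanism.** Multiple imputation in its standard form is justified under MAR. The plan reserves it for data judged MNAR, where it carries the bias forward unless the imputation model states how unseen values differ from seen ones.
2. **The trigger.** Below 10%, the amount missing decides the mechanism, but a proportion says nothing about why values are missing. Above 10%, further analyses come first. They cannot supply the classification that the imputation sentence relies on, because MAR and MNAR cannot be told apart from observed data.
3. **No replacement with repeated measures ANOVA.** In its standard form this model drops a participant who misses one assessment. A MAR label does not justify complete-case analysis, and the result no longer covers everyone randomised.

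What is at stake is the primary comparison. Reasons for missing data that differ by arm are plausible here. The Discussion says that withdrawal may worsen disease control and lead to a drug being restarted, and the Procedure section warns deprescribed participants about returning symptoms and withdrawal reactions.

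**Working it through.** **Inputs from the Sample size calculation section.** Mean change at 12 months −1.9 (SD 4.1) with intervention and +0.1 (SD 3.5) with control, so a difference of −2.0; two-sided 95% confidence; 80% power; 58 per group; 20% attrition; 70 per arm.

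**The plan's own figure.** Mean variance = (4.1² + 3.5²)/2 = (16.81 + 12.25)/2 = 14.53. Then n = 2 × 14.53 × (1.960 + 0.8416)² / 2.0² = 2 × 14.53 × 7.849 / 4 = 57.02, rounded up to 58 per group. The stated 58 reproduces, so the planning inputs are read correctly. How 58 was inflated to 70 is a separate matter.

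**Which branch may apply.** 20% of 140 is 28 missing, above the 10% line (14 of 140). If attrition as planned carries over to the medication count, the over-10% branch applies.

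**What the 10% line allows.** It is set per outcome variable, not per arm. Up to 13 of 140 (9.3%) could be missing and still be declared MAR. In the extreme case that all 13 are in the intervention arm, that is 13/70 = 18.6% of the arm.

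**Illustration of MNAR.** Assume that 20% of the intervention arm drop out and return to their baseline count, that nothing seen before dropout signals this, and that control dropouts resemble control completers.

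- True difference = (0.8 × −1.9 + 0.2 × 0) − 0.1 = −1.52 − 0.1 = −1.62, about 1.6 in size.
- Complete cases, imputation under MAR and a mixed model under MAR all give about −1.9 − 0.1 = −2.0.
- Gap: about 0.4 medications.

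**Simulation of method against mechanism.** 400,000 per arm, with the means and SDs above. Assumed, not from the documents: correlation 0.6 between 3- and 6-month change; 60% of the mean change reached by 3 months; in the intervention arm, log-odds of a missing 6-month value rising by 1 per SD towards a smaller reduction, driven by the seen 3-month change (MAR) or the unseen 6-month change (MNAR); control values missing completely at random. True difference −2.0.

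| Mechanism | Missing | No replacement | Imputation under MAR |
|---|---|---|---|
| MAR | 5% | −2.12 | −2.01 |
| MAR | 9.9% | −2.22 | −2.00 |
| MAR | 20% | −2.42 | −1.99 |
| MNAR | 5% | −2.19 | −2.12 |
| MNAR | 9.9% | −2.37 | −2.25 |
| MNAR | 20% | −2.71 | −2.47 |

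Imputation removes the bias under MAR, where the plan's only stated instruction (below 10%) is not to impute. It leaves about 0.12 to 0.47 medications under MNAR, the only case in which the plan says to impute. The sign follows from the assumed direction of dropout and is not evidence about this trial.

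**Range without a mechanism.** If unseen values in one arm differ on average from the imputed ones by d medications, bias = proportion missing × d. For an assumed d of 1 to 4, this is 0.05 to 0.20 at 5% missing, 0.10 to 0.40 at 9.9% and 0.20 to 0.80 at 20%.

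**The case against.** Several points on the other side have weight.

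- **Imputation can be run under MNAR**, for example with a delta adjustment, and such detail may sit in an analysis plan that is not shown. That is true. The error is in the stated allocation: imputation is assigned to MNAR data only, no departure model is named, and no stated rule uses it under MAR.
- **No replacement under MAR is sound with a likelihood-based model.** Also true. The weakness is its combination with repeated measures ANOVA. That participants are dropped is inferred from that pairing; the text does not say so.
- **The authors may have meant not missing completely at random.** Possibly, but the sentence as printed would still need correcting.
- **The EMR may fill the count when a call is missed.** This stands. It may keep missingness of the primary outcome below the planned attrition. It does not repair the rule, which also covers adherence collected by telephone and falls collected by diary.

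A reader might infer three stronger things that the documents do not support. One is that the reduction in medications is bound to be overstated. That needs intervention dropouts to do worse than those who stay, and the Discussion says only that drugs may be restarted, not that such patients leave the study. Another is that the gap of 0.4 is the price of this rule compared with a better one. It is the price of MNAR under any MAR-based method, including the mixed model recommended below. The last is that the number of complete rows per arm can be predicted. The documents give no rate of missed 3-month assessments and do not say what happens to data over 10% missing that are judged MAR.

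**Conclusion.** The rule is wrong as written, and the fault lies in stated text, not in omitted detail. It matches imputation to the mechanism for which its standard form is not valid, relies on a cut-off that cannot establish MAR, and with standard repeated measures ANOVA leaves a complete-case analysis under an intention-to-treat heading.

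The estimate can be biased; it cannot be said that it will be. Size and direction depend on an unknown mechanism, and below 10% missing the bias may be small. With the 20% attrition that the plan assumes, the over-10% branch may well apply to the primary outcome. The illustrative contrast of about 1.6 against about 2.0 rests on a 12-month effect, whereas follow-up here is 6 months, and on full return to baseline among intervention dropouts. Its use is to show why an MNAR sensitivity analysis is needed, because no MAR-based primary analysis would reveal that gap.

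**What to change.** Delete the 10% threshold and the sentence that assigns multiple imputation to MNAR data. Put in their place:

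- **Primary analysis.** A likelihood-based mixed model for repeated measures using all randomised participants with any follow-up count; or multiple imputation by arm, with the baseline and 3-month counts in the imputation model. Either is stated to hold under MAR and is used whatever the percentage missing.
- **Sensitivity analyses, prespecified.** Delta-adjusted (tipping-point) imputation for MNAR, and an analysis that assumes return to the baseline count for intervention-arm dropouts.

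The cost is a few sentences and a little more analysis work, with no change to sample size or data collection. Mixed models are available in the named software. The sensitivity results may look slightly less favourable. The change should be made before outcome data are seen.

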**Fig 1 pone.0324565.g001:**
[figure not shown]
Flowchart on the five-steps of the physical-pharmacy partnership in deprescribing intervention.

The researcher will review potential participant’s electronic medical records (EMR), if available, on the day before their appointment. The researcher will first approach the physician attending to the potential participant to determine suitability for the study before approaching selected potential patients to explain the purpose of the study. If the individual agrees to participate in the study, they will be randomised to an intervention (deprescribing) or control group (usual care) in a 1:1 ratio using a computerized random number generator in Microsoft Office® Excel® (Washington, United States of America) [24]. Participants randomized to the control group will continue to receive usual care, where medications will be reviewed and prescribed by their physician. Meanwhile, patients in the intervention group will receive an in-depth medication review performed by a pharmacist, which will focus on identifying PIMs as opportunities for deprescribing. In the intervention arm, a registered pharmacist will perform medication reconciliation using a structured medication list. However, in the control group, physicians will rely on electronic medical records and routine medication history-taking. PIMs identified in the intervention group will be deprescribed using the P3ID intervention, as shown in Participants will be followed up over 6 months (Fig 2). To assess the primary outcome, the number of prescribed medications will be determined by reviewing the patient’s medications through EMR and patient interviews via telephone calls at 3 months and 6 months. Medication adherence will be assessed using PMAI-9 and HMAI-9 via telephone calls at 3 months and 6 months. All participants will be requested to record any adverse drug reactions (ADR) due to their prescribed medications. For those undergoing deprescribing, they will be informed about the potential of withdrawal-related adverse effects, such as the return of previous symptoms or other withdrawal reactions. They will be asked to monitor and record any such symptoms. and asked to record these symptoms or withdrawal reactions. They will also be advised to see a doctor if they feel unwell or notice any unexpected adverse effects after stopping the medication.

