### Outcome measures

The primary outcome of this study will be the total number of prescribed medications. Secondary outcomes measured will include the number of medications deprescribed, fall occurrence, falls rate, PMAI-9 and HMAI-9. Within the intervention arm, additional information will be obtained on PIM, number of PIM deprescribed, and patients’ and doctors’ satisfaction towards pharmacist services.

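### The primary analysis is a repeated measures ANOVA with no deciding effect or visit named, and it does not match the change-from-baseline comparison that sized the trial

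*Protocol article*

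**What the plan says.** Under Outcome measures: "The primary outcome of this study will be the total number of prescribed medications". No time point is attached, and the text does not say whether the level or the change is meant.

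Under Procedure, the count comes from the medical record and "patient interviews via telephone calls at 3 months and 6 months"; neither visit is ranked. Also there: "Participants will be followed up over 6 months".

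Under Data analysis, the second paragraph introduces the primary outcome as continuous and continues: "Between-group and within-group analyses will be conducted using repeated measures analysis of variance". The first paragraph states more generally that, for follow-up comparisons, "the independent t-test will be used for continuous variables". On adjustment: "Unadjusted analyses will first be presented". Confounders are to be chosen later, and the baseline medication count is not named among them.

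Under Sample size calculation, the trial is sized on the "mean change in the number of prescribed medications at 12 months", −1.9 ± 4.1 against +0.1 ± 3.5, which is a two-sample comparison of change.

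Table 1 lists the patient assessment form, which includes medication history, at baseline, 3 months and 6 months.

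**The concern.** A two-arm repeated measures ANOVA yields a group effect, a time effect and a group-by-time effect. These answer different questions and have different power. The protocol names the method but not the effect that decides the trial.

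Two things are at stake. First, the 80% power was calculated for a difference in change from baseline. A group main effect that averages over a pre-randomisation baseline tests a smaller quantity, because the expected difference at baseline is zero. A comparison of raw follow-up counts ignores the baseline count and so carries all the between-patient variation. Second, if more than one effect or visit can be presented as the primary result, the 5% error rate no longer applies.

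The within-group part adds a further risk of misreading. Change inside one arm is not a randomised comparison. Everyone is enrolled with at least one potentially inappropriate medication and has a medication review at the clinic, so counts may fall in both arms.

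**Working it through.** **Inputs from the protocol article.** Difference in mean change: 0.1 − (−1.9) = 2.0. SDs of change: 4.1 and 3.5. Two-sided 5%, 80% power, 70 recruited per arm, 20% attrition.

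**Assumptions (not in the document).** Correlation ρ between any two medication counts of 0.5 to 0.8, equal at all pairs of visits; equal SD at every visit; true difference 0 at baseline.

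**1. The plan's own figure.** Pooled SD of change = √((4.1² + 3.5²)/2) = 3.81. n per arm = 2 × [3.81 × (1.960 + 0.842)/2.0]² = 57.02, rounded up to 58. The stated 58 reproduces, for a change-score test. With 70 × 0.8 = 56 evaluable per arm, that test has about 79% power.

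**2. SD of the raw count.** Since SD of change = s√(2(1 − ρ)), s = 3.81/√(2(1 − ρ)): 3.81, 4.26, 4.92 and 6.03 at ρ = 0.5, 0.6, 0.7 and 0.8.

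**3. Effect and SD under each reading** (difference of 2.0 at both 3 and 6 months):
- Group main effect over baseline, 3 and 6 months: effect (0 + 2 + 2)/3 = 1.33; SD s√((1 + 2ρ)/3) = 3.11, 3.65, 4.40, 5.61.
- Group effect over 3 and 6 months only: effect 2.0; SD s√((1 + ρ)/2) = 3.30, 3.81, 4.54, 5.72.
- Raw t-test at 6 months: effect 2.0; SD s.
- Baseline-adjusted comparison at 6 months: effect 2.0; SD s√(1 − ρ²) = 3.30, 3.41, 3.51, 3.62.
- Group-by-time F test over three visits (2 numerator df): non-centrality (n/2) × Σ(d − d̄)²/(s²(1 − ρ)). As s²(1 − ρ) = 3.81²/2 = 7.265, this does not depend on ρ. Constant effect: 28 × 2.667/7.265 = 10.28. Effect growing 0, 1, 2: 28 × 2/7.265 = 7.71.

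**4. Power at 56 per arm, two-sided 5%:**

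| Reading | ρ 0.5 | 0.6 | 0.7 | 0.8 |
|---|---|---|---|---|
| Group effect, baseline included | 61% | 48% | 36% | 24% |
| Group effect, 3 and 6 months only | 89% | 79% | 64% | 45% |
| Raw t-test at 6 months | 79% | 69% | 57% | 41% |
| Group-by-time, constant effect | 82% | 82% | 82% | 82% |
| Group-by-time, effect 0, 1, 2 | 69% | 69% | 69% | 69% |
| Baseline-adjusted, 6 months | 89% | 87% | 85% | 83% |

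**5. Type I error when the choice is open.** In null simulations (20,000 trials per correlation), the chance that the group effect or the group-by-time effect is significant is about 10%. If t-tests at 3 and 6 months may also be claimed, it is about 12% to 14%.

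**The case against.** A reader might infer that the ANOVA certainly dilutes the effect. The document does not establish this. Dilution needs baseline to be a repeated level and the group main effect to be the deciding test. The within-group analysis and Table 1 imply the first but do not state it, and Procedure lists only the 3- and 6-month assessments for the primary outcome. With those two visits alone, a constant effect is not diluted; power is lost at higher correlations because baseline is unused.

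A reader might also infer that none of the named analyses reaches 80%. That is wrong. The group-by-time test, a standard output of the same ANOVA, has about 82% under a constant effect. But the text does not select it, and it falls to about 69% if the effect builds up over time.

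Nor is the t-test clearly a rival primary test. Its sentence stands in a general paragraph, and the later sentence on the primary outcome most naturally overrides it. The 12% to 14% error rate therefore needs a looser reading; about 10% is the figure for the ANOVA alone.

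Adjusted analyses are foreseen, so adjustment is not excluded, and an unseen analysis plan may list covariates. That part stands. It does not remove the problem: the protocol fixes a method that differs from its sizing basis, and which visit and contrast decide the trial belongs with the definition of the primary outcome. Finally, the one-point shortfall from 80% to 79% at 56 per arm comes from the attrition allowance, not from the analysis.

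**Conclusion.** The point holds in conditional form. The protocol article commits to a repeated measures ANOVA, unadjusted in the first instance, without naming the deciding effect or visit, and sizes the trial on a different quantity. Depending on the reading, power for the planned difference of 2.0 at both visits runs from 24% to 89% at 56 per arm. The lowest figures belong to the group main effect with baseline included. Type I error is about 10% if either ANOVA effect may be called primary.

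The power figures rest on an assumed correlation of 0.5 to 0.8 with equal correlations and SDs across visits, and should be read as a range. The averaging of 2.0 to 1.33 does not depend on the correlation, only on baseline being a level and the effect being constant. The sizing source reports change at 12 months while follow-up here is 6; all figures take the 2.0 as given.

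**What to change.** State one primary test before outcome data are seen: the between-arm difference in number of prescribed medications at 6 months, adjusted for baseline count, two-sided 5%. Either ANCOVA at 6 months, or a mixed model for the 3- and 6-month counts with arm, visit, arm-by-visit and baseline count, would serve. Label the 3-month difference, the other ANOVA effects and any unadjusted t-tests as supportive, and within-arm change as descriptive.

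Naming the group-by-time contrast at one visit would also remove the ambiguity. Baseline adjustment is preferable because, under the assumptions above, its variance relative to a change score is (1 + ρ)/2, that is 0.75 to 0.90.

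The cost is wording only, since Table 1 already provides for medication history at all three times. The one thing given up is the option of promoting the 3-month result to primary.

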**Conclusion:**

The P3ID trial tests the hypothesis that a jointly led pharmacist-physician intervention in an outpatient will reduce the total number of medications, improve medication adherence, reduce falls and improve patients’ and doctors’ satisfaction towards pharmacist services. Findings from this study would inform future deprescribing practices, particularly in LMIC, pertaining to fall prevention as well as aid the development of future deprescribing interventions in other settings.

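### The adherence scores are taken at baseline, but no stated analysis makes the baseline PMAI-9 or HMAI-9 score a covariate, so precision may be lost

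*Protocol article*

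**What the plan says.** The Abstract's Conclusion lists better adherence among the hypotheses ("improve medication adherence, reduce falls"). Outcome measures places both scales among the secondary outcomes: "Secondary outcomes measured will include the number of medications deprescribed, fall occurrence, falls rate, PMAI-9 and HMAI-9". The Procedure section says "Medication adherence will be assessed using PMAI-9 and HMAI-9 via telephone calls at 3 months and 6 months", and Table 1 gives the time points of each instrument as "Baseline, 3 month, 6 month". Table 1 does not restrict them to one arm, and they are not in the list of items collected only in the intervention arm.

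The Data analysis section offers two routes for such scores. For comparisons of follow-up data, "the independent t-test will be used for continuous variables". Later in the section, outcomes measured once go to regression and "those with multiple measurements with repeated measures analysis of variance or general estimating equations. Unadjusted analyses will first be presented". The next sentence says that potential confounders will be chosen from published evidence and clinical judgement. The baseline adherence score is neither named as a covariate nor ruled out.

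**The concern.** A baseline score on the same scale usually carries information about the follow-up score. In a randomised comparison, conditioning on it leaves the treatment contrast unchanged and removes variance that has nothing to do with treatment. The stated routes do not secure this gain:

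- The follow-up t-test does not use the baseline score at all.
- Repeated measures ANOVA over three visits takes the baseline score as one of the responses. The article itself says that baseline differences would be random, so that visit holds no treatment effect. The between-group effect then averages two treated visits with one untreated visit.
- Adjustment for confounders does not ensure inclusion. Under 1:1 randomisation the baseline score is a prognostic covariate, used for precision. Someone selecting confounders need not pick it.

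At stake is power for a stated secondary hypothesis, lost although the baseline scores are already scheduled.

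**Working it through.** **The plan's own figure.** The sample size concerns the medication count only. With a difference of 2.0 and SDs of 4.1 and 3.5, n = (4.1² + 3.5²)(1.960 + 0.842)² / 2.0² = 57.02, so 58 per arm, as stated. The article gives no power figure for adherence.

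**Inputs.**
- From the Sample size calculation section: 70 recruited per arm and 20% attrition, so 70 × 0.8 = 56 per arm; two-sided 5% level.
- Assumed, because the documents give nothing: a true effect of 0.5 SD at both 3 and 6 months, equal variances, and the same correlation r between any two visits, with r = 0.3, 0.5 and 0.7.

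**Formulas** (SD set to 1, d the standardised effect; power from the noncentral t or F distribution).
1. Follow-up t-test at 6 months: d = 0.5, noncentrality 0.5 × √(56/2) = 2.65.
2. ANCOVA at 6 months: the residual variance is 1 − r², so d = 0.5/√(1 − r²) = 0.524, 0.577, 0.700.
3. ANOVA between-group effect over three visits: the mean effect is (0 + 0.5 + 0.5)/3 = 0.333 and the variance of a patient's mean is (1 + 2r)/3, so d = 0.333/√((1 + 2r)/3) = 0.456, 0.408, 0.373.
4. ANOVA group-by-time test (2 and 220 df): the effects 0, 0.5, 0.5 have a centred sum of squares of 0.1667, so the noncentrality is 28 × 0.1667/(1 − r) = 6.67, 9.33, 15.56.
5. ANCOVA on the mean of the 3- and 6-month scores: the residual variance is (1 + r)/2 − r².

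**Power.**

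| Analysis | r = 0.3 | r = 0.5 | r = 0.7 |
|---|---|---|---|
| t-test, 6 months | 75% | 75% | 75% |
| ANOVA between-group effect, three visits | 67% | 57% | 50% |
| ANOVA group-by-time | 63% | 78% | 95% |
| ANCOVA, 6 months | 78% | 86% | 96% |
| ANCOVA, mean of 3 and 6 months | 94% | 96% | 99% |

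The variance of the t-test comparison relative to ANCOVA is 1/(1 − r²) = 1.10, 1.33 and 1.96. At r = 0.2 the gain almost vanishes: 75% for the t-test against 76% for 6-month ANCOVA.

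At each of the three correlations, ANCOVA at 6 months has more power than the t-test and either ANOVA test. The between-group effect falls below even the plain t-test.

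**The case against.** **Baseline may yet be used.** Saying that unadjusted results come first implies that adjusted ones follow, and those could include the baseline score. A GEE of the two follow-up visits with baseline as a covariate also fits the text. A reader might infer that the plan rules out conditioning on baseline, but it does not. What stands is that nothing secures it.

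**The group-by-time test already uses baseline.** It works as a change-type comparison, and at r = 0.7 it is one point behind ANCOVA (95% against 96%). The 67%, 57% and 50% figures apply only if the between-group effect is read as the treatment result, and the article does not say that it will be. This stands, so the dilution is conditional.

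**The gain rests on an unknown correlation.** This stands too. At low r the t-test loses little.

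**A stronger reading is tempting.** Two instruments at two follow-up visits make four comparisons with none singled out, so a reader might infer that error control is lost. The documents do not support that:
- Adherence is secondary, and the article promises no error control for secondary outcomes.
- Naming one key instrument and visit is commonly left to the statistical analysis plan, which is not shown.
- Four tests arise only if each visit is tested separately. ANOVA or GEE can give one test per instrument, at most 1 − 0.95² = 9.75% for two independent tests.
- The often-quoted 1 − 0.95⁴ = 18.5% counts false results in both directions. A false claim of improvement on at least one of four tests has probability 1 − 0.975⁴ = 9.6% if they are independent, and about 6.5% at a between-test correlation of 0.7.

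**Conclusion.** The point holds as one of precision. The article schedules baseline adherence scores, then states a follow-up comparison that ignores them and repeated-measures methods that do not name them as a covariate. Under the assumptions above, baseline adjustment raises 6-month power from 75% to between 78% and 96%. The ANOVA between-group effect including baseline would lower it to between 67% and 50%. These sizes depend on an assumed effect, an assumed correlation and equal correlation between visits. The direction of the ANCOVA gain over the t-test needs only a correlation clearly above zero. The consequence is limited to a secondary outcome. No loss of error control is shown, and the plan need not rank the two instruments or the two visits on this account.

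**What to change.** State in Data analysis that the 3- and 6-month PMAI-9 and HMAI-9 scores will be compared between arms with the same instrument's baseline score as a covariate, either by ANCOVA or by a mixed model or GEE in which only the follow-up visits are responses. Add that the adherence conclusion will not rest on the unadjusted follow-up t-test or on an ANOVA between-group effect that includes the baseline visit. Unadjusted results can still be shown descriptively.

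The cost is a few sentences of analysis text, settled before outcome data are examined. It needs no extra patients, visits or data, and the model uses one further parameter per instrument. If the statistical analysis plan already says this, a pointer to it is enough.
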